### Sample/participants

#### Participants

The patients will be recruited from the Oncology Hospitalisation Unit at the CAUSA, and must meet the following selection criteria: A) Inclusion criteria: Participants must have a pathological diagnosis of an oncological disease, be over 18 years of age, be hospitalised at the time of recruitment in the Oncology Unit at CAUSA, meet dyspnoea parameters of 2 or more points on the Medical Research Council scale (MRC), receive fewer than 85 points on the Barthel Index, and have signed an informed consent form indicating voluntary agreement to participate in the study. B) Exclusion criteria: not having an adequate cognitive state to be able to comprehend and follow the orders provided (fewer than 23 points on the Mini Mental State Examination, MMSE), having a haemoglobin level lower than 10 g/dL, being an active smoker at the time of recruitment. C) Withdrawal criteria: disease progression which brings the patient to a terminal situation or to death, and non-completion of the follow-up and final assessments.

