#### Sample size

The sample size has been estimated based on the potential modification of the most stringent of the principal variables of the study—the score on the Barthel Index. For this, as a reference, we have used the results obtained in a study with similar characteristics, in which the scoring on the Barthel Index was modified by 7.5 points [17]. With these premises, accepting an alpha risk of 0.05 and a beta risk of 0.2 in a bilateral contrast, we will need 25 subjects in the first group and 25 subjects in the second group in order to detect a difference greater than or equal to 7.5 units. The assumed common standard deviation is 8.3. We estimate a rate of 20% lost to follow-up. The sample size was estimated using the programme EPIDAT 4.2.

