### Procedures and data collection

#### Evaluations and study plan

Three assessments will be completed in this study: one at the beginning, another after 7 days, and a final one before the patient is discharged from hospital. After recruitment and before randomisation and assignment to the corresponding group, all individuals will complete a baseline assessment (BA), which includes recording the independent variables and the variables of the primary and secondary results of the study. Then, while the patients are still in hospital, the subjects will be randomly assigned to the control or the experimental group, with the corresponding intervention applied in each of them. Later, two more assessments will be completed, one after 7 days, considered to be the follow-up assessment (FUA), and another at the time of discharge from the hospital, considered to be the final assessment (FA). This can be observed in more detail in Table 1.

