### Data analysis

The statistical analysis will be carried out with the intention to treat. In the descriptive analysis, the population is described by presenting the data as means and standard deviations for the continuous variables and as frequency distributions for the qualitative variables. To evaluate the comparability in the baseline assessment between the two study groups, we will employ the Chi-squared test for qualitative variables and the Student’s T-test for the comparison of the means between the two groups, in addition to the Kolmogorov–Smirnov test to find the normality of the sample. In the inferential analysis, we will consider a confidence interval of 95% (*p* < 0.05), and will use Student’s T-test for related pre and post samples and for independent samples at the end of the study, in addition to a multivariate analysis of variance (MANOVA) with repeated measures (3 levels) to assess interactions between categorical variables, and to determine significant differences between groups and within groups. Additionally, to assess the magnitude of the change in the variables, the effect size of the interventions will be calculated as Cohen’s d (small (0.2), medium (0.5), and large (0.8)) and the partial eta squared (ƞ2p) (small (0.01), medium (0.06), and large (0.14)), where significant, as appropriate with the statistical test applied [25]. We will use Pearson’s Correlation Coefficient to analyse the correlations between the various intervening variables and the parameters established in the different questionnaires and scales employed. A survival follow-up analysis will be completed using the Kaplan–Meier non-parametric method to learn the time of the intervention until the patient’s discharge from hospital, and the survival curves of each of the groups in the study will be compared using the non-parametric logrank test. Processing and analysing the data will be done using the statistics pack SPSS 25.0.

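### The withdrawal criteria and the three-level repeated-measures MANOVA, applied as written, give a completer comparison that would be reported as intention to treat

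*Protocol article*

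**What the plan says.** Under Participants, the article says that patients "must meet the following selection criteria" and then gives three lists: inclusion (A), exclusion (B) and withdrawal (C). The third reads: "Withdrawal criteria: disease progression which brings the patient to a terminal situation or to death, and non-completion of the follow-up and final assessments".

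Under Evaluations and study plan, baseline is assessed before randomisation and the other two assessments come after it: "Later, two more assessments will be completed, one after 7 days, considered to be the follow-up assessment (FUA), and another at the time of discharge".

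Under Data analysis, the population is fixed in one sentence: "The statistical analysis will be carried out with the intention to treat". The methods named for the outcomes are a paired t-test before and after, an independent-samples t-test at the end of the study, and a "multivariate analysis of variance (MANOVA) with repeated measures (3 levels").

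Under Sample size, the article plans 25 patients per group and estimates 20% lost to follow-up.

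**The concern.** Intention to treat means that what happens after allocation does not decide who is analysed. Here a patient's status in the study depends on exactly such events. Death and terminal progression could be read as reasons why participation ends. Missing an assessment is different, because it is not a treatment decision. As a criterion, its only evident use is to mark who has usable data.

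The repeated-measures MANOVA works in the same direction, since a patient without a value at any one of the three time points drops out of it. The rule and the method together produce a completer set, while the stated principle promises the randomised set.

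The population makes this more than a formality. Participants are in hospital with cancer, dyspnoea of at least 2 on the MRC scale and a Barthel Index below 85, and the Background notes that dyspnoea in advanced disease may signal its final phase. Deterioration and death are foreseeable and plausibly related to both primary outcomes. A patient who dies in hospital has no discharge assessment. If the arms lose different kinds or numbers of patients, randomisation no longer protects the comparison.

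**Working it through.** **1. Set the statements side by side.**

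| Event | When it can occur | Withdrawal criterion? | Effect on the three-level MANOVA | Effect on the end-of-study t-test |
|---|---|---|---|---|
| Terminal progression | After randomisation | Yes | Out if any assessment is missing | Out if no final value |
| Death in hospital | After randomisation | Yes | Out | Out (no discharge value) |
| Day-7 or discharge assessment missed | After randomisation | Yes (unclear whether missing one is enough, or both) | Out | Out only if the discharge value is missing |
| Discharged before day 7, with discharge assessment | After randomisation | Depends on that same reading | Out (no day-7 value) | Can be included |

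**2. Reproduce the plan's sample size.** Inputs, all from the Sample size section: difference 7.5, SD 8.3, two-sided alpha 0.05, power 0.80, loss 20%.

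- n per arm = 2 × (SD/difference)² × (1.960 + 0.842)² = 2 × (8.3/7.5)² × 7.849 = 19.2, rounded up to 20.
- Allowing for loss: 20/(1 − 0.20) = 25 per arm, as stated.

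The plan is therefore sized for about 20 evaluable patients per arm, with about 5 of 25 lost per arm (10 of 50). Exact t-test power is 79.5% with 20 per arm and 87.9% with all 25.

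**3. Illustrate the possible bias.** The documents give neither the reason for loss nor its split by arm, so everything here except the SD of 8.3 is assumed:

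- There is no true effect.
- Patients with the worst latent prognosis are the ones lost.
- Barthel score = 65 + 6U + 5.7e, with U and e standard normal. The SD is √(36 + 32.49) = 8.28, close to the planned 8.3.
- Loss is governed by 0.8U + 0.6e′, with e′ an independent standard normal. Its covariance with the Barthel score is 6 × 0.8 = 4.8, so the correlation is 4.8/8.28 = 0.58.

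If a fraction p is lost, the completers' mean rises by 4.8 × λ(p), where λ(p) = φ(Φ⁻¹(p))/(1 − p). The spurious difference is 4.8 × [λ(p₁) − λ(p₂)].

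| Loss by arm | λ(p₁) | λ(p₂) | Spurious difference (points) | As % of 7.5 |
|---|---|---|---|---|
| 20% / 20% | 0.350 | 0.350 | 0 | 0 |
| 25% / 15% | 0.424 | 0.274 | 0.72 | 10 |
| 30% / 10% | 0.497 | 0.195 | 1.45 | 19 |

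Simulation of the same model gave 0.67 and 1.47 for the last two rows.

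The result depends on the assumed correlation. With SD 8.3 and a correlation from 0.3 to 1, 30%/10% loss gives 0.75 to 2.5 points, and a milder 24%/16% split gives 0.3 to 1.0. In this model the shift works against the arm that keeps more patients. Loss of patients who recover and go home early would act the other way and is not modelled.

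**The case against.** The strongest reply is that withdrawal need not mean exclusion from analysis. The only sentence that defines the analysis population says intention to treat, and death necessarily ends follow-up under any plan. Details of missing-data handling may also sit in a fuller document. This stands in part: removal of withdrawn patients from the analysis set is a strong inference, not stated text. It does not dispose of the point, because the article itself names a method that discards incomplete patients and makes non-completion a withdrawal ground. This is a conflict within the text, not a missing detail.

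A reader might be tempted by three stronger readings that the document does not support.

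- *Every outcome analysis is confined to patients who stayed a week and left hospital alive.* The paired and end-of-study t-tests can use a patient discharged before day 7 who has baseline and discharge values, unless the withdrawal rule is read as triggered by missing either assessment. The wording leaves that open.
- *The expected 20% will be lost because of their outcome.* The Sample size section gives a rate and no reason. Allowing for loss is compatible with intention to treat.
- *The trial will be underpowered because of this.* The plan already assumes 20 evaluable patients per arm, with power of about 80%. The documents give no higher loss rate from which to derive a shortfall.

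It is also fair to say that equal loss in the two arms, of the same kind of patient, produces no bias, and that the direction of any bias cannot be derived from the document.

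**Conclusion.** The point holds as a conflict between the withdrawal criteria, the named repeated-measures method and the stated intention-to-treat principle. Followed as written, the repeated-measures comparison is of completers and would carry the wrong label. That conclusion rests on the wording and on how the method treats missing values, not on the simulation.

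The size of the consequence is uncertain. About 10 of 50 patients are expected to be lost. Under assumed prognosis-related loss that differs by arm, the Barthel difference moves by roughly 0.7 to 1.5 points, or 10% to 20% of the target; with equal loss it does not move. These figures show scale only. The conflict should be resolved before any unblinded analysis, because choosing the population afterwards in a 50-patient trial would not be credible.

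**What to change.** 1. Delete non-completion of the follow-up and final assessments as a withdrawal ground.
2. State that withdrawal, or stopping the programme, does not remove a patient from the analysis set, and that all randomised patients are analysed in their assigned arm. This concerns the analysis set only; when a patient should stop the programme is a clinical matter and is not addressed here.
3. Replace the complete-case repeated-measures MANOVA with a mixed model for repeated measures on all available assessments (arm, visit and arm-by-visit). Enter baseline as one of the outcome time points. With baseline as a covariate, a patient with no later value would contribute no outcome record and would again be left out.
4. Pre-specify a sensitivity analysis for death and terminal progression, for example one that ranks death as the worst Barthel outcome. Other approaches are defensible; what matters is that one is fixed in advance.
5. If these changes are not made, drop the intention-to-treat label and describe the analysis as one of completers.

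The cost is protocol and analysis wording. Visits, sample size and software stay the same, since SPSS fits mixed models. The downside is that the main model relies on data being missing at random, which is questionable when loss follows deterioration or death. The sensitivity analysis probes that assumption but does not remove it.

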#### Sample size

The sample size has been estimated based on the potential modification of the most stringent of the principal variables of the study—the score on the Barthel Index. For this, as a reference, we have used the results obtained in a study with similar characteristics, in which the scoring on the Barthel Index was modified by 7.5 points [17]. With these premises, accepting an alpha risk of 0.05 and a beta risk of 0.2 in a bilateral contrast, we will need 25 subjects in the first group and 25 subjects in the second group in order to detect a difference greater than or equal to 7.5 units. The assumed common standard deviation is 8.3. We estimate a rate of 20% lost to follow-up. The sample size was estimated using the programme EPIDAT 4.2.

#### Sample assignment

After meeting the selection criteria listed above and being recruited for the study, the individuals will be assigned via a simple randomisation process to one of the two conditions of the study: Experimental Condition or Control Condition. As detailed in Fig. 1.

**Fig. 1 Fig1:**
[figure not shown]
Flow Chart of the study. The enrolled participants are to be randomly assigned to one of the study conditions, with assessments to be taken at three pre-specified time points

#### Randomisation

We will employ a simple randomisation process, which consists of generating a table of random numbers that is the same size as the estimated sample in the study. This will be done using Microsoft Excel 2020. Each of the randomised numbers will be assigned a condition: for even numbers, the subject will be assigned to the Experimental condition, and for odd numbers, they will be assigned to the Control condition. The work of the randomisation sequencing, the recruitment of participants, and of assigning them to a group will be completed by research personnel who are not related to the assessments nor to the implementation of the intervention, which will prevent potential biases in the study.

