### Design

This study is an experimental, prospective, randomized, parallel-controlled clinical trial, with two arms design of fixed assignment with an experimental and a control groups. It will conduct during a year in the Oncology Hospitalisation Unit at the University Hospital Complex of Salamanca (CAUSA), using consecutive sampling to select the participants with oncological dyspnoea who are hospitalised at the time of inclusion.

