#### Blinding

Given the nature of the intervention, the participating subjects will not be blinded. However, to minimise any contamination between groups, the investigator responsible for the measurements of the study at each assessment and for the statistical analysis will be blinded, thus increasing the scientific quality in the study process.

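### List generation, recruitment and assignment are given to the same group with no concealed release described, so the next allocation may be known when patients are approached

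*Protocol article*

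**What the plan says.** The Randomisation section of the protocol article fixes four things.

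- **Sequence.** Simple randomisation, by "generating a table of random numbers that is the same size as the estimated sample in the study". On the tool it says: "This will be done using Microsoft Excel 2020".
- **Decoding.** The arm follows from parity: "for even numbers, the subject will be assigned to the Experimental condition, and for odd numbers, they will be assigned to the Control condition".
- **Who does it.** "The work of the randomisation sequencing, the recruitment of participants, and of assigning them to a group will be completed by research personnel".
- **The safeguard claimed.** These are personnel "who are not related to the assessments nor to the implementation of the intervention, which will prevent potential biases in the study".

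Other sections bear on the point. Design describes recruitment as "using consecutive sampling to select the participants with oncological dyspnoea who are hospitalised at the time of inclusion". Evaluations and study plan puts the baseline assessment after recruitment and before randomisation. Blinding and Limitations blind the investigator who measures and analyses, but not the participants, and do not mention the recruiting personnel. No section describes sealed envelopes, a central service or a list held by someone outside recruitment.

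**The concern.** Randomisation protects the comparison only if the person deciding whether and when to enrol a patient cannot foresee the arm. The separation that secures this is between whoever holds the list and whoever recruits. The protocol puts those two tasks in the same group. It then presents a different separation, from assessment and treatment, as what prevents bias.

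A recruiter who can see the next arm may, without intending to, approach a fitter or more motivated patient when the next place is experimental, or wait a day with a frailer one. The arms would then differ in prognosis at entry. Blinded assessment would measure that difference faithfully but could not remove it. In a trial of 50 patients on one hospital unit, it would also be hard to detect afterwards.

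**Working it through.** **1. Which bias each stated measure addresses.**

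| Measure in the article | What it protects | Does it hide the next arm from the recruiter? |
|---|---|---|
| Sequence and recruitment staff do not assess (Randomisation) | Outcome measurement | No |
| Sequence and recruitment staff do not deliver treatment (Randomisation) | Delivery of care | No |
| Assessor and analyst blinded (Blinding, Limitations) | Outcome measurement, analysis | No |
| Baseline before assignment (Evaluations and study plan) | Baseline scores | No; the approach to the patient has already happened |
| Consecutive sampling (Design) | Limits choice of patient | No; it limits what could be done with the knowledge |

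No row separates the list from the recruiter.

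**2. Can the arm be read from the list?** Yes. The table is as long as the planned sample and parity gives the arm, so whoever holds it can read every remaining allocation. Whether the recruiter holds it is not stated.

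**3. The plan's own sample size.** Inputs from Sample size: difference 7.5 Barthel points, SD 8.3, two-sided alpha 0.05, power 0.80, loss 20%.

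n per arm = 2 × (1.960 + 0.842)² × (8.3/7.5)² = 2 × 7.849 × 1.2247 = 19.2, rounded up to 20. Allowing for loss, 20/0.80 = 25 per arm. This matches the stated 25, so 20 per arm is the expected number analysed after loss.

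**4. Illustration of the consequence.** Assume no treatment effect, and that selective enrolment shifts the mean outcome between arms by d standard deviations. The article gives no value for d, so a range is shown. For the two-sided independent-samples t-test at the end of the study, the noncentrality is d × √(n/2). The rejection rate is the probability that a noncentral t with 2n − 2 degrees of freedom falls outside ±2.024 (n = 20, 38 df) or ±2.011 (n = 25, 48 df).

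| d (assumed) | Barthel points (d × 8.3) | Share of the 7.5 target | Noncentrality, n = 20 | False-positive rate, n = 20 | False-positive rate, n = 25 |
|---|---|---|---|---|---|
| 0 | 0 | 0% | 0 | 5.0% | 5.0% |
| 0.10 | 0.83 | 11% | 0.316 | 6.1% | 6.4% |
| 0.25 | 2.08 | 28% | 0.791 | 12.0% | 13.9% |
| 0.50 | 4.15 | 55% | 1.581 | 33.8% | 41.0% |

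These rates apply to the unadjusted end-of-study t-test named in Data analysis. They do not describe the repeated-measures MANOVA planned alongside it.

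**The case against.** A reader might infer that the recruiter knows every allocation in advance and that the trial has no allocation concealment. The article does not support that. It refers to research personnel, who may be several people dividing the three tasks, and nowhere says that one individual does all three or that the recruiter can see the list. It is also a journal article, and a concealment step may be described in a full protocol that is not shown. Silence about envelopes is not by itself a finding.

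The article also contains real restraints:

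- Under consecutive sampling, a recruiter who follows the rule does not choose among eligible patients.
- Eligibility rests mostly on scores and measurements (MRC, Barthel, MMSE, haemoglobin), which narrows discretion.
- The baseline assessment precedes assignment and is made by a blinded investigator.
- Simple randomisation has no blocks, so past allocations reveal nothing about the next one to someone without the list.

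On size, the shifts are assumed, all run in one direction and carry fully into the endpoint. In the repeated-measures analysis, a stable baseline difference would not by itself appear as a group-by-time effect. That participants are unblinded says nothing about what recruiters can foresee.

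All of this stands as a limit on how strongly the point can be put. It does not dispose of the point. The grouping of tasks is stated, not omitted, and is offered as protection against bias. Envelopes would not conceal a list from the people who wrote it, so a concealment step in the full protocol would still have to be reconciled with this sentence. Consecutive sampling leaves the timing and manner of the approach, and of seeking consent, to the recruiter. The repeated-measures analysis does not remove differences in expected recovery or motivation.

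**Conclusion.** The point holds as a badly fixed rule. The article gives list generation, recruitment and assignment to the same group, uses a pre-made list readable by parity, and describes no concealed release. The next allocation may therefore be known to those who decide whom to approach and when. Separation from assessment and treatment does not protect against this, so the claim that it prevents bias is not supported. Consecutive sampling and baseline before assignment reduce the risk without removing it.

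The size cannot be fixed from the documents. Under the assumed shifts, the consequence for the unadjusted end-of-study t-test runs from negligible (about 6% at 0.10 SD) to serious (about 34% at 0.50 SD). The conclusion does not depend on any one of these values. It should be corrected before recruitment, because selection at enrolment cannot reliably be undone in the analysis.

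**What to change.** Change the Randomisation section so that an existing team member with no role in recruitment generates and holds the list. State that each allocation is released to the recruiting staff only through a concealed mechanism: sequentially numbered, opaque, sealed envelopes prepared by that person, or a locked electronic list. Release should follow recorded consent and baseline assessment. The order of those steps is already planned, so the only new elements are the independent list-holder and the concealed release. Replace the claim that the present arrangement prevents bias with a statement of what each separation protects against.

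If the tasks are already divided in practice, correcting the text to say so and naming the release mechanism is enough.

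Cost: reassigning tasks within the team and preparing 50 envelopes or an electronic list, with no extra staff or visits.
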